### Methods of Randomization, Concealment and Blinding

The randomization sequence will be created at a single central location at the Epidemiology and Research Coordinating Centre (EPICORE) at the University of Alberta (available at: http://www.epicore.ualberta.ca/index.html). This randomization sequence will be stratified by the presence of a diagnosis of sepsis. The clinical trial pharmacist (unblinded) will use a web-based randomization program to determine allocation of patients and then prepare the coded study solution. Each coded study solution bag will then be dispensed for administration to the patient as per protocol. This coded identifying study number will also be labeled on the patient CRF. The investigators, study coordinators, treating physicians, bedside nurses and patients/family will remain blinded to the allocated study solution.

### Data Collection

Detailed clinical, procedure-related, physiologic and laboratory data will be collected. Blood and urine will be collected at baseline, 12 hours, 24 hours and daily thereafter until participants exits the study. Data will be collected on standardized CRFs developed by the EPICORE centre. Completed CRF will be returned to the EPICORE centre, entered into a central database, where data queries will be generated.

Clinical data captured will include demographics, co-morbidities and prescribed/current drug therapy. Details of admission diagnoses, surgical status, and dates of hospital and ICU admission will be recorded. Detailed data will be recorded on date of enrollment (i.e. fulfilling criteria for early AKI). This will include details of interventions (i.e. mechanical ventilation, vasoactive drugs, fluid therapy), hemodynamics (i.e. blood pressure, heart rate, central venous pressure), and acute physiology (i.e. components of severity of illness scores, urine output, fluid balance, secondary non-kidney organ dysfunction). During the trial, data will be collected daily on urine output, fluid balance, electrolytes, acid-base status, serum creatinine and urea. Collected blood and urine samples will be stored for batched analysis of kidney-injury specific biomarkers, including: serum and urine cystatin C, serum and urine neutrophil gelatinase-associated lipocalin (NGAL), urine interleukin-18 (IL-18); urine kidney injury molecule-1 (KIM-1), and urine L-type fatty acid binding protein (L-FABP).

Data will be collected each day on whether the primary endpoint (progression of AKI) has occurred, for evidence of any secondary endpoints and for criteria for trial discontinuation.

Finally, any study protocol violations will be recorded. The adjudication of protocol violations will be determined by a study investigator blinded to the treatment allocation.

All enrolled patients will be followed to determine the duration of AKI, continued need for RRT, renal recovery and mortality until death or discharge from hospital and at 30, 60 and 90-days after randomization.

### Sample Size Estimation

Our primary outcome measure for this trial is progression from early AKI (RIFLE class - **RISK**) to a more severe form of AKI, defined by progression in AKI to the development of either RIFLE class - **Injury or Failure**. Based on data from a large observational study, an estimated 60% of critically ill patients with early AKI worsen and develop further kidney injury[46]. We estimate that furosemide will contribute to a 20% absolute reduction in the proportion of those patients who progress from early AKI (RIFLE class - **RISK**) to either RIFLE class - **Injury or Failure**. This would require a total sample size of 214 patients and provide 80% power (alpha 0.05) for detection of a 20% difference in the proportion with progression of AKI. An estimated 50% of patients developing early AKI will have sepsis[47]. Randomization will be stratified by the presence of sepsis. The total sample size was increased to 216 patients to ensure a balanced number of patients in each treatment arm (Figure 1).

### Statistical Analysis

The primary analysis will evaluate the proportion of critically ill patients with early AKI that have progression in kidney injury by having received furosemide or placebo. Analysis will be intention-to-treat.

The secondary analysis will evaluate for differences between furosemide and placebo in cumulative fluid balance and in the largest changes to serum potassium, serum magnesium, serum pH and serum bicarbonate levels, defined as difference from enrollment to lowest documented level during study infusion. In addition, this secondary analysis will evaluate for differences in the need for RRT, duration of AKI, rate of renal recovery and hospital mortality.

Descriptive statistics, boxplots and histograms will be used to analyze individual baseline variables by having received furosemide or placebo. Normally or near normally distributed, non-correlated variables will be reported as means with standard deviations (SD) and compared using the appropriate Student's t test. Non-normally distributed, non-correlated continuous data will be reported as medians with inter-quartile ranges (IQR) and compared using the Mann Whitney U test. Non-correlated categorical data, including the primary outcome, and need for RRT, renal recovery and hospital mortality, will be reported as proportions and compared using Fisher's Exact Test. If necessary, multi-variable logistic or linear regression will be used to control for potential confounding from imbalances in baseline characteristics after randomization.

The tertiary analysis will evaluate for differences between furosemide and placebo in the change of novel serum and urine biomarkers for AKI, defined by absolute levels and relative to baseline (enrollment) at 12 hours, 24 hours and at the time of initiation of RRT, renal recovery or ICU discharge. All samples will remain blinded during processing, storage and analysis. Normally distributed correlated data will be analyzed by the repeated measures ANOVA. Non-normally distributed correlated data will be analyzed by the Friedman test. Correlated categorical data will analyzed by generalized estimating equations. The diagnostic and predictive characteristics of absolute values and relative changes in novel serum and urine biomarkers for progression of AKI as well as need for RRT will be evaluated by 2 x 2 tables and construction of receiver operator characteristic curves. A p-value of < 0.05 will be considered significant. All statistical tests will be two-sided.

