≥95	0.4 mg/kg	0.05 mg/kg/hr	4.8	1.2

An estimate of patient ideal body weight (IBW) will be used to determine the urine output target. Determination of estimated IBW will be based on the formula described by Devine[45] (Table 2). From this estimated IBW, patients will be divided into 5 kg weight categories to determine urine output goals for protocol simplicity (Table 3). At any time during the trial, if the responsible ICU physician believes that the administration of furosemide is urgently indicated (i.e. new pulmonary edema), it can be administered and this event will be documented.

**Table 2 T2:** Devine formulate for ideal body weight estimation[45].

Sex	Devine Formula				
Female	IBW (kg) = [45 +(0.91 x (height in cm - 152))]				

Male	IBW (kg) = [50+ (0.91 x (height in cm - 152))]				

					

**Height (cm)**	**Height (feet)**	**Female**		**Male**	
		
		**IBW (kg)**	**Category**	**IBW (kg)**	**Category**

≤152	≤5'0	45	≤50	50	≤50

155	5'1	47.7	≤50	52.7	55

157	5'2	49.6	≤50	54.6	55

160	5'3	52.3	55	57.3	60

163	5'4	55.0	55	60.0	60

165	5'5	56.8	60	61.8	65

168	5'6	59.6	60	64.6	65

170	5'7	61.4	65	66.4	70

173	5'8	64.1	65	69.1	70

175	5'9	65.9	70	70.9	75

178	5'10	68.7	70	73.7	75

180	5'11	70.5	75	75.5	80

183	6'0	73.2	75	78.2	80

185	6'1	75.0	75	80.0	80

188	6'2	77.8	80	82.8	85

191	6'3	80.5	85	85.5	90

193	6'4	82.3	85	87.3	90

196	6'5	85.0	85	90.0	90

≥ 198	≥ 6'6	86.9	90	91.9	95

**Table 3 T3:** Summary of weight-based urine output targets.

Weight Category (kg)	Target Urine Output (mL)			
	
	Hourly	Per 6 hours	Per 12 hours	Per 24 hours
≤50	50-100	300-600	600-1200	≥ 1200

55	55-110	330-660	660-1320	≥ 1320

60	60-120	360-720	720-1440	≥ 1440

65	65-130	390-780	780-1560	≥ 1560

70	70-140	420-840	840-1680	≥ 1680

75	75-150	450-900	900-1800	≥ 1800

80	80-160	480-960	960-1920	≥ 1920

85	85-170	510-1020	1020-2040	≥ 2040

90	90-180	540-1080	1080-2160	≥ 2160

≥ 95	95-190	570-1140	1140-2280	≥ 2280

All other aspects of patient management within the parameters outlined (i.e. methods of fluid resuscitation, choice of fluids, vasoactive therapy, choice of vasoactive therapy, adjuvant therapies such as hrAPC, intensive insulin therapy) will be at the discretion of the consultant ICU physician. No other interventions will be performed.

The study drug infusion will be continued for a minimum of 24 hrs and discontinued if any one of the following events occurs:

• The patient is initiated on RRT;

• The patient is discharged from the ICU;

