• The patient recovers kidney function;

• The patient dies;

• The patient develops a recognized adverse reaction potentially related to the study infusion; or

• The patient has received a total of 7-days of study drug administration.

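### The electrolyte and acid-base endpoint is labelled largest change but scores only the lowest on-infusion value, which attenuates rises and ties the comparison to infusion length

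*Protocol article*

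**What the plan says.** The Statistical Analysis section of the protocol article places these laboratory measures in the secondary analysis. Arms are to be compared "in the largest changes to serum potassium, serum magnesium, serum pH and serum bicarbonate levels", with the change "defined as difference from enrollment to lowest documented level during study infusion". Continuous variables go to a t test or a Mann-Whitney test, two-sided. Regression is held in reserve for imbalance in baseline characteristics; infusion duration is not mentioned.

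The measurement window is therefore the infusion. Study Intervention states: "The study drug infusion will be continued for a minimum of 24 hrs and discontinued if any one of the following events occurs". The listed events include "The patient is initiated on RRT", "The patient is discharged from the ICU", "The patient recovers kidney function", death, an adverse reaction, and the upper limit, "The patient has received a total of 7-days of study drug administration".

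Three other places bear on the point:

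- Data Collection has blood drawn at baseline, 12 hours, 24 hours and then daily, and has electrolytes and acid-base status recorded daily.
- Potential Challenges with the Trial names low magnesium and low potassium as common with furosemide.
- The RRT definition lists hyperkalemia among the criteria for starting RRT, together with low pH and low bicarbonate.

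**The concern.** There are two separate faults in the one rule.

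**Direction.** A largest change can go either way; a lowest level looks only downward. Suppose a patient's potassium rises by an amount *a* and at another time falls by a smaller amount *b*. The label promises +*a* and the definition records −*b*. The protocol itself treats high potassium as important, so rises are not irrelevant to it.

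**Length.** The lowest of several fluctuating readings becomes lower, on average, the more readings there are. The number of readings is set by how long the infusion ran, which is decided after randomisation by events the trial also studies as outcomes: RRT, renal recovery and mortality. If treatment alters any of these, the arms are sampled for different lengths of time. The sign cannot be predicted. Faster recovery on furosemide would shorten its window and make its nadirs look shallower, whereas delayed RRT would lengthen the window and make them look deeper. A difference between arms could thus be created or hidden without any effect on the analyte.

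**Working it through.** **The plan's own figures.** The article gives no figure for this endpoint. Its sample size reproduces: 60% versus 40%, two-sided alpha 0.05 and 80% power give 97 per arm without continuity correction and 107 with it, and 2 × 107 = 214, raised to 216. Only the 108 per arm is used below.

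**Number of readings.** On the 12 h, 24 h, then daily schedule, a 1-day infusion gives 2 post-baseline readings, 2 days give 3, 3 days give 4, 4 days give 5, and 7 days give 8. One extra reading is one extra day.

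**Length dependence with no drug effect.** The measure is D = min(X₁, …, X_k) − X₀. All readings have the same mean and an SD of 1, and are normal with first-order autocorrelation ρ. The article gives neither ρ nor the infusion durations. I took ρ = 0, 0.5 and 0.8 as assumptions and simulated.

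| ρ | Mean D, 4 readings | Mean D, 5 readings | Shift | SD of D (4; 5) | t test rejection, 4 vs 5 |
|---|---|---|---|---|---|
| 0 | −1.03 | −1.17 | 0.14 | 1.22; 1.21 | about 12% |
| 0.5 | −0.81 | −0.95 | 0.14 | 1.09; 1.10 | about 15% |
| 0.8 | −0.55 | −0.66 | 0.11 | 0.81; 0.85 | about 15% |

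Hand check at ρ = 0.5:

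- Standard error = √((1.09² + 1.10²)/108) = 0.149.
- The shift before rounding is 0.135, so z = 0.135/0.149 = 0.91.
- Rejection probability ≈ P(Z > 1.96 − 0.91) + P(Z < −1.96 − 0.91) ≈ 0.147 + 0.002, or about 15%. This agrees with the simulation.

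With 4 readings in both arms the test rejects 4 to 5% of the time, as it should. With 3 versus 4 it rejects about 19 to 25%, and with 3 versus 5 about 47 to 59%.

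**What happens to a rise.** If every post-baseline reading in one arm is shifted up by 1 SD, the minimum moves up by exactly 1 SD, so the arms differ by the full amount. If the rise instead climbs linearly in time to 1 SD at the last reading, the minimum tends to come from the early readings and the arms differ by only 0.42 to 0.48 SD over the same range of ρ.

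**The case against.** The strongest reply is that the minimum was chosen for a reason. Low magnesium and low potassium are the harms that the article attributes to furosemide. For pH and bicarbonate, its RRT criteria single out the low side. Measuring on infusion is a legitimate way to look for disturbance caused by the drug. High potassium also reaches the analysis in part through need for RRT. Daily values are collected, so nothing is lost from the data. This stands as a defence of the nadir for potassium and magnesium and of keeping an on-infusion summary. It does not reconcile the label with the definition, and it does not answer the dependence on duration.

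Three stronger readings are tempting, and the documents do not support them.

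- A reader might infer that the endpoint is blind to a rise such as a diuretic alkalosis. It is not: the difference can be positive, the tests are two-sided, a sustained rise comes through in full and a gradual one at a little under half. The article nowhere mentions alkalosis.
- A reader might compare 2 readings with 7 and, with independent readings and an assumed within-patient potassium SD of 0.4 mmol/L, obtain (1.35 − 0.56) × 0.4 = 0.32 mmol/L. That needs every patient in one arm to have 2 readings and every patient in the other to have 7. Nothing in the article suggests such a gap. At the same assumed SD, one extra reading is worth 0.11 × 0.4 to 0.14 × 0.4, or about 0.04 to 0.06 mmol/L.
- A reader might take this as the trial's main safety comparison. The article lists electrolyte and acid-base balance as a secondary endpoint and names safety separately in the Abstract.

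**Conclusion.** The point holds as a fault of definition in a named secondary endpoint. The label and the rule disagree on the face of the text. Gradual rises are attenuated, which matters most for pH, bicarbonate and high potassium. The comparison between arms is confounded with infusion duration: about 0.11 to 0.14 SD, and a 5% test running at about 12 to 15%, for one extra reading in one arm.

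Those sizes rest on assumed normal readings, assumed correlation of 0 to 0.8, a common number of readings within each arm, and the schedule in Data Collection. Routine ICU tests, if they count as documented levels, would change the counts. The actual bias depends on a between-arm difference in duration that the article does not give; if durations turn out equal, there is none from this source. No conclusion about the primary outcome or the sample size follows.

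**What to change.** Reword the secondary analysis along these lines:

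- **Measures.** Keep the lowest value for potassium and magnesium, and add the highest value for potassium, pH and bicarbonate. The lowest pH and bicarbonate already defined may stay. Name each measure for what it is, in place of largest change.
- **Window.** Make the main comparison over one window of fixed length from randomisation, the same for all patients whether or not the infusion is still running, adjusted for the enrollment value. Fix the length before unblinding. The window matters for the added measures too, because a highest value climbs with the number of readings just as a lowest one falls.
- **Values after RRT, ICU discharge or death.** State how each is handled. RRT may itself alter these analytes.
- **Supportive analysis.** Keep the on-infusion nadir, reported beside infusion duration by arm, and say whether time with the infusion paused for excess diuresis counts as on infusion.

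The cost is a change of wording and slightly more analysis. It needs no new assay, because daily values are already planned, and it touches no clinical rule. There are two drawbacks. Nadirs after the fixed window are left to the supportive analysis. The sponsor must also confirm that daily collection continues once the infusion stops, which the article does not make clear. A longitudinal model of the daily values is a reasonable extra but is not needed to repair the rule.

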**Design/Methods:**

This protocol summarizes the rationale and design of a phase II randomized, blinded, placebo-controlled trial of a low-dose continuous infusion of furosemide, titrated to the physiology parameter of urine output, in critically ill patients with early AKI. Two hundred sixteen adult critically ill patients with early evidence of AKI, defined by the RIFLE criteria, will be enrolled. Included patients will also have fulfilled ≥2 criteria of the systemic inflammatory response syndrome and achieved immediate goals of acute resuscitation. The primary outcome is progression in severity of kidney injury. Secondary outcomes include: safety, fluid balance, electrolyte balance, the need for renal replacement therapy, duration of AKI, rate of renal recovery, mortality and changes in novel serum and urine biomarkers of AKI. The primary analysis will be intention-to-treat. Planned recruitment will be complete by June 2011 and results available by December 2011.

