## Objectives

The specific objectives of this trial are:

• To compare the efficacy and safety of a continuous infusion of furosemide versus placebo titrated to the physiology parameter of urine output in early AKI on the primary outcome of progression in severity of kidney injury from early AKI.

• To evaluate the impact of furosemide versus placebo on key secondary endpoints including: fluid balance; electrolyte and acid-base balance; the need for RRT; total duration of AKI; the rate of renal recovery; and mortality.

• To evaluate the impact of furosemide versus placebo on the tertiary endpoint of differences, trajectory and prognostic value of novel serum and urine biomarkers for AKI.

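### Mortality status is collected at 30, 60 and 90 days after randomization, but the only mortality measure given an analysis is hospital mortality, whose window closes at discharge

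*Protocol article*

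**What the plan says.** The Data Collection section of the protocol article sets the follow-up. It covers everyone randomized: "All enrolled patients will be followed to determine the duration of AKI, continued need for RRT, renal recovery and mortality". It runs to hospital exit and also to three fixed times: "mortality until death or discharge from hospital and at 30, 60 and 90-days after randomization".

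The Statistical Analysis section names the mortality outcome twice. The list of secondary comparisons ends with "rate of renal recovery and hospital mortality". In the sentence on categorical outcomes, "need for RRT, renal recovery and hospital mortality, will be reported as proportions and compared using Fisher's Exact Test".

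The Objectives give the outcome without a time window, ending the list of secondary endpoints with "total duration of AKI; the rate of renal recovery; and mortality". The Abstract does the same: "duration of AKI, rate of renal recovery, mortality and changes in novel serum and urine biomarkers of AKI". No section assigns an analysis by name to vital status at day 30, 60 or 90.

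**The concern.** Hospital mortality counts each patient for as long as that patient stays in hospital. Someone discharged alive on day 10 is a survivor whatever happens on day 20; someone still an inpatient on day 20 who dies then is a death. Discharge comes after randomization, and the treatment could affect its timing.

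The Background gives some reason not to dismiss this. The systematic review it cites found a shorter duration of RRT with loop diuretics (weighted mean difference -1.4 days, p = 0.02). It had too little data to comment on fluid balance, duration of ventilation or hospital length of stay. An effect on discharge timing is therefore neither shown nor excluded.

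What is at stake is how the mortality result reads. The same review reports a mortality odds ratio of 1.28 (p = 0.18), so harm is an open question. The Discussion hopes the trial will help design a phase III study powered on an outcome such as RRT or mortality. Mortality at a fixed time from randomization serves that purpose better than a rate with a variable window. If no time point is named in advance, a later choice among three would be post hoc.

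**Working it through.** **1. Setting the sections side by side**

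| Section | Mortality measure | Window |
|---|---|---|
| Abstract | mortality | not stated |
| Objectives | mortality | not stated |
| Data Collection | mortality, all enrolled patients | to death or discharge, and days 30, 60, 90 |
| Statistical Analysis, secondary list | hospital mortality | to discharge |
| Statistical Analysis, categorical data | hospital mortality, Fisher's exact test | to discharge |

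The article is not silent on the mortality analysis. It fixes the measure and the test, and the measure it picks leaves the fixed-time data without a named use.

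**2. The plan's own figure**

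The article states no figure for mortality. Its only sample size is for AKI progression: 60% against 40%, 80% power, two-sided alpha 0.05, 214 in total.

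- Uncorrected: n = [1.96 × √(2 × 0.5 × 0.5) + 0.8416 × √(0.6 × 0.4 + 0.4 × 0.6)]² / 0.2² = 96.9, so 97 per arm (194 in total).
- With continuity correction: (96.9 / 4) × [1 + √(1 + 4 / (96.9 × 0.2))]² = 106.7, so 107 per arm, or 214.

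The stated figure is reproduced. It does not depend on how mortality is defined.

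**3. Deaths that fall outside the hospital window (assumed inputs)**

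Per arm: 216 / 2 = 108. Let h be hospital mortality and q the share of those discharged alive who die by day 90; neither is in the document. Deaths left out per arm = 108 × (1 − h) × q.

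- h = 0.5, q = 0.05: 108 × 0.5 × 0.05 = 2.7
- h = 0.3, q = 0.10: 108 × 0.7 × 0.10 = 7.6

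This counts omitted deaths. It is not a measure of bias, because the same omission in both arms need not distort the comparison.

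**4. What a difference in discharge timing could do (assumed inputs)**

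Let true 90-day mortality m be equal in the two arms, and let s be the share of those deaths that occur before discharge. Hospital mortality is then m × s, ignoring in-hospital deaths after day 90. The last column is the exact probability of a two-sided Fisher p below 0.05 at 108 per arm.

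| m | s, arm A / arm B | Hospital mortality A / B | Difference (points) | P(p < 0.05) |
|---|---|---|---|---|
| 30% | 0.9 / 0.9 | 27% / 27% | 0 | 3.4% |
| 30% | 0.9 / 0.8 | 27% / 24% | 3 | 5.8% |
| 30% | 0.9 / 0.7 | 27% / 21% | 6 | 13.8% |
| 40% | 0.9 / 0.9 | 36% / 36% | 0 | 3.7% |
| 40% | 0.9 / 0.8 | 36% / 32% | 4 | 7.4% |
| 40% | 0.9 / 0.7 | 36% / 28% | 8 | 20.0% |
| 50% | 0.9 / 0.9 | 45% / 45% | 0 | 3.4% |
| 50% | 0.9 / 0.8 | 45% / 40% | 5 | 8.7% |
| 50% | 0.9 / 0.7 | 45% / 35% | 10 | 27.4% |

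In every row day-90 mortality is equal by construction, so any difference shown comes from the window alone. The same mechanism, in the other direction, could mask a true difference.

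**The case against.** The best reply is that the article does not exclude fixed-time analyses. The sentence on Fisher's test introduces its list with the word *including*, so the list can be read as examples. Death by day 30, 60 or 90 is uncorrelated categorical data to which the same test would apply. The article is also a condensed account, and an analysis plan that is not shown may tabulate every time point. This stands, and it limits the point. A reader might infer that the sections contradict each other, or that the 30-, 60- and 90-day data will go unanalysed; the document supports neither. What remains is that hospital mortality is the only mortality measure the article names for analysis, and it names it twice.

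Second, hospital mortality is well defined, can be analysed as written and needs no tracing after discharge. The assurance about losses to follow-up in Potential Challenges with the Trial covers only the intervention period, so day-90 status could be missing for some discharged patients. This also stands. It is a reason to report missing status by arm and to keep hospital mortality as supportive. It does not remove the dependence on discharge.

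Third, the illustration rests wholly on assumptions. Nothing in the document supports a gap of 10 or 20 points between arms in the share of deaths before discharge. That is correct, and the table shows a mechanism, not an estimate.

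Fourth, mortality is one of several secondary outcomes in a phase II trial sized on AKI progression. That is why the point is minor.

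**Conclusion.** The point holds as a minor one. Vital status at three fixed times is to be collected for all enrolled patients, while the mortality measure tied to an analysis in this article has a window that ends at an event treatment could influence. A fixed-time measure from randomization, built on data already planned, is the better main mortality analysis.

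The size of any bias cannot be derived from the document. Under the assumed inputs above it ranges from none, if discharge timing is alike in the arms, to a probability of 13.8 to 27.4% of a nominally significant difference with no difference in 90-day mortality; that upper range needs a 20-point gap that nothing in the text supports. A reader might go further and conclude that the planned mortality comparison is biased, or that hospital mortality should be dropped. Neither follows: no effect on discharge timing is documented, and hospital mortality remains a legitimate measure. The primary analysis and the sample size of 216 are unaffected.

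**What to change.** In the Statistical Analysis section, name one fixed-time measure as the main mortality analysis. For example:

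> The main mortality analysis will compare all-cause mortality at day 90 after randomization between the randomized arms, using the test given for other categorical outcomes. Hospital mortality will be reported as a supportive measure. The number of patients with unknown day-90 status will be reported by arm.

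Day 30 or day 60 would also remove the dependence on discharge. What matters is that one time is chosen before allocation is unblinded. If an analysis plan already does this, the article's wording needs only to agree with it. The defect does not call for survival curves or adjustment for sepsis.

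The cost is a change of wording, with no new visits, data or patients. The one downside is possible missing fixed-time status for some discharged patients. This is a cheap improvement of minor severity.

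### The four electrolyte and acid-base change scores are compared without adjusting for the enrolment value: valid, but less precise than a baseline-adjusted analysis that costs almost nothing

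*Protocol article*

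**What the plan says.** All of this stands in the protocol article, mostly under Statistical Analysis.

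- **Endpoint form.** The secondary analysis takes the largest change in serum potassium, magnesium, pH and bicarbonate, "defined as difference from enrollment to lowest documented level during study infusion". Each is therefore a change score.
- **Tests.** Normal or near-normal non-correlated variables are "compared using the appropriate Student's t test"; non-normal ones are "compared using the Mann Whitney U test". Neither test takes a covariate.
- **Adjustment.** The only provision is conditional: "If necessary, multi-variable logistic or linear regression will be used to control for potential confounding from imbalances in baseline characteristics after randomization". No trigger and no covariates are named.
- **Availability of the enrolment value.** Under Data Collection: "Blood and urine will be collected at baseline, 12 hours, 24 hours and daily thereafter". The change score cannot be formed without the enrolment value, so every analysable patient has one.
- **Biomarkers are handled separately.** They are "defined by absolute levels and relative to baseline (enrollment) at 12 hours, 24 hours", and repeated data get their own methods: "Normally distributed correlated data will be analyzed by the repeated measures ANOVA" and "Non-normally distributed correlated data will be analyzed by the Friedman test".

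**The concern.** How far a patient's potassium or bicarbonate falls depends partly on where it started: a high enrolment value tends to come down whatever the treatment. A raw change score subtracts the whole enrolment value. Unless the regression of the follow-up value on the enrolment value has slope 1, this over- or under-corrects and carries the noise of the enrolment reading into the comparison. A model with the enrolment value as a covariate estimates that slope from the data.

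The Objectives section puts safety in the first objective and electrolyte and acid-base balance among the key secondary endpoints. The section on potential challenges expects low magnesium and potassium to be common with furosemide. An imprecise comparison makes a real difference between arms on these measures easier to miss. The conditional regression does not meet this point. It responds to imbalance seen after randomisation, whereas adjustment for the enrolment value gains precision even when the arms are balanced.

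**Working it through.** **1. The plan's own figure.** The inputs, from Sample Size Estimation and Statistical Analysis, are 60% versus 40% progression, 80% power and two-sided α 0.05. The uncorrected two-proportion formula gives

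n = [1.96·√(2·0.5·0.5) + 0.8416·√(0.6·0.4 + 0.4·0.6)]² / 0.2² = (1.386 + 0.583)² / 0.04 ≈ 96.9, so 97 per arm (194 in total).

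The continuity correction gives

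(96.9/4)·[1 + √(1 + 4/(96.9·0.2))]² ≈ 106.7, so 107 per arm, or 214.

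The stated 214 (raised to 216) is reproduced. It concerns the primary outcome only; what follows uses just 108 per arm, assuming equal allocation.

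**2. Variances.** Let enrolment and follow-up values both have SD 1 and correlation ρ. Per patient:

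- change score: 1 + 1 − 2ρ = 2(1 − ρ)
- ANCOVA: 1 − ρ²
- ratio: (1 − ρ²) / [2(1 − ρ)] = (1 + ρ)/2

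**3. Numbers.** The documents give no ρ, so a range is shown. The detectable difference at 80% power is 2.80·√(2v/108), where v is the per-patient variance. The equivalent N is 216 × ratio, the number of patients with which ANCOVA matches a 216-patient change-score analysis. The last column is Φ(2.80/√ratio − 1.96), the ANCOVA power for an effect that the change-score test detects with 80% power.

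| ρ (assumed) | Ratio | Detectable, change (SD) | Detectable, ANCOVA (SD) | Equivalent N | ANCOVA power |
|---|---|---|---|---|---|
| 0.3 | 0.65 | 0.451 | 0.364 | 140 | 94% |
| 0.5 | 0.75 | 0.381 | 0.330 | 162 | 90% |
| 0.7 | 0.85 | 0.295 | 0.272 | 184 | 86% |
| 0.9 | 0.95 | 0.170 | 0.166 | 205 | 82% |

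**4. Unequal variances.** If the follow-up SD is k times the enrolment SD, the change-score variance is 1 + k² − 2ρk and the ANCOVA variance is k²(1 − ρ²). The difference is 1 − 2ρk + ρ²k² = (1 − ρk)², which is never negative. The size of the gain changes with k, but its direction does not. It vanishes only when ρk = 1, that is, when the slope is 1.

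**5. The endpoint as written.** The lowest of a variable number of values is not a single follow-up reading, so the ratio in step 2 is approximate. A simulation took the lowest of 1 to 7 daily values, with 108 per arm, exchangeable correlation ρ and 2000 replicates. It compared the t test on change with a linear model on arm and enrolment value:

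| Effect (assumed) | ρ 0.3 | ρ 0.5 | ρ 0.7 |
|---|---|---|---|
| 0.3 SD | 47% vs 67% | 65% vs 79% | 86% vs 91% |
| 0.5 SD | 91% vs 99% | 97% vs 99.5% | 100% vs 100% |

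An independent run at 0.3 SD gave 50% vs 70%, 62% vs 76% and 85% vs 91%. At ρ 0.9 and 0.3 SD, both methods are at about 100%.

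**The case against.** **The planned comparison is valid.** This stands. A reader might infer that ignoring the enrolment value biases the result or inflates false positives. It does neither: under randomisation the change-score comparison is unbiased and keeps its type I error. A chance enrolment difference makes a particular estimate less precise, and that is all.

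**The size rests on chosen inputs.** This also stands. Both ρ and the effect size are assumptions, and the protocol sets no power target for these endpoints, so no stated design property fails. At a 0.5 SD effect, or at ρ near 0.9, there is little left to gain.

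**Regression is already allowed, and covariate lists belong in an analysis plan.** This stands only in part. The regression clause is triggered by imbalance and is not the planned estimator. The article also goes beyond silence, since it names both the endpoint form and the test. Changing the main estimate therefore means changing a stated method.

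**Biomarkers.** A reader might extend the point and say that biomarkers, too, get unadjusted t tests on raw levels or changes. The text does not support that. The t-test sentence is limited to non-correlated variables, and repeated data go to repeated measures ANOVA or the Friedman test. Enrolment may enter that ANOVA as a time level, and levels relative to baseline are also planned. No power figure is therefore claimed here for biomarkers.

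**Conclusion.** The point holds as a precision loss on four secondary endpoints: potassium, magnesium, pH and bicarbonate. It is an almost free improvement to a stated method, not an error that threatens validity. Adjusting for the enrolment value cuts the variance by about 35%, 25%, 15% and 5% at ρ of 0.3, 0.5, 0.7 and 0.9, assuming equal variances and treating the lowest value approximately as a single follow-up value. In power terms, at ρ 0.5, this is about 14 points for a 0.3 SD effect and about 2 points for 0.5 SD. The direction does not depend on these assumptions, but the size does. These figures describe the t test; with Mann-Whitney on skewed data they would differ somewhat. The primary Fisher comparison and the sample size of 216 are not touched.

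**What to change.** For potassium, magnesium, pH and bicarbonate, state that the main between-arm estimate comes from a pre-specified linear model. The outcome is the lowest value during infusion; the terms are arm, enrolment value and sepsis stratum. Use a log or rank scale if a measure is strongly skewed. On the untransformed scale, modelling the change score with the same covariates gives the same arm estimate apart from sign, so the endpoint definition can stay. Keep the t test or Mann-Whitney U test as a descriptive check.

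For biomarkers, the parallel change is optional: a repeated-measures model of the follow-up values, log-transformed where suitable, with the enrolment value as covariate.

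The cost is wording, one or two model degrees of freedom, and a transformed scale for skewed measures. No new data are needed.
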